#### Secondary Outcomes

Secondary outcome measures include multiple efficacy and patient-reported outcomes assessed at weeks 0, 1, 2, and 4, specifically the proportions of patients achieving EASI75 (≥75% improvement in EASI score from baseline) and EASI90 (≥90% improvement in EASI score from baseline), the IGA, the Dermatology Life Quality Index (DLQI), BSA, the Pruritus Numeric Rating Scale (PNRS), the Patient-Oriented Eczema Measure (POEM), and changes in TCM syndrome scores from baseline. The complete study protocol, including detailed information on the secondary outcome measures and assessment time points, is presented in Table 3.

##### Investigator Global Assessment

The IGA score is a simplified assessment based on the investigator’s subjective judgment that allows for a rapid evaluation of overall disease severity [13]. At each study visit, investigators assess the patient’s global disease manifestations using a 6-point scale ranging from 0 to 5. The scoring criteria are defined as follows: 0 (clear, no inflammatory signs), 1 (almost clear, minimal residual erythema or papulation), 2 (mild erythema with slight papulation or induration), 3 (moderate erythema with definite papulation or induration), 4 (severe erythema with marked inflammatory lesions), and 5 (very severe, with extensive or confluent erythema and prominent exudation or crusting). One of the outcome measures is the proportion of patients who achieve an IGA score of 0 or 1 with an improvement of at least 2 points from baseline. Longitudinal IGA assessments are performed at baseline (week 0) and at weeks 1, 2, and 4 after treatment initiation.

##### Dermatology Life Quality Index

The DLQI is used to systematically assess patients’ quality of life over the previous week, covering multiple domains including physical symptoms, psychological well-being, family relationships, interpersonal communication, occupational limitations, social activities, and treatment-related impact [14]. The DLQI uses a 4-point severity scoring system for each of the 10 items, resulting in a total score ranging from 0 to 30, with higher scores indicating poorer quality of life. In this study, DLQI will be assessed at baseline (week 0) and at weeks 1, 2, and 4 after treatment initiation.

##### Body Surface Area

BSA is a commonly used clinical indicator for assessing skin disease severity [15]. In this assessment, the area of a patient’s single palm, including the volar surface of the fingers, is defined as 1% of the total BSA. The extent of skin lesions is estimated by calculating how many “palm areas” are involved across the whole body, and changes in the percentage of affected BSA are evaluated relative to baseline. In this study, BSA will be assessed at baseline (week 0) and at weeks 1, 2, and 4.

##### Pruritus Numerical Rating Scale

The PNRS is a single-item patient-reported scale used to assess the severity of pruritus in patients with AD [16]. It uses a 0 to 10 visual analog scale, where 0 indicates no itch and 10 indicates the most severe itch, and patients mark the scale themselves at each visit. In this study, PNRS scores will be assessed at baseline (week 0) and at weeks 1, 2, and 4.

##### Patient-Oriented Eczema Measure

POEM is a repeatable patient-reported outcome measure used to assess the severity of AD [17]. It evaluates the frequency of 7 symptoms experienced over the previous week, including pruritus, sleep disturbance, bleeding, oozing, skin cracking, scaling, and dryness or roughness. Each item is scored from 0 to 4 according to symptom frequency, yielding a total score ranging from 0 to 28, with higher scores indicating more severe disease. In this study, POEM scores will be assessed at baseline (week 0) and at weeks 1, 2, and 4.

##### TCM Syndrome Scores

The TCM syndrome score is assessed using a graded quantitative method based on the local and systemic symptoms of wind-damp-heat stagnation syndrome. The assessment of local symptoms primarily includes the severity of pruritus and the color of skin lesions, each scored on a 4-point scale from 0 to 3, corresponding to absent, mild, moderate, and severe, respectively. For skin lesion sites (head and neck, trunk, upper limbs, lower limbs, and special areas) and skin lesion types (erythema; papules or maculopapules; vesicles; exudation; scales; crusts; hypertrophy, roughness, or lichenification; and hyperpigmentation), each item is scored on a 2-point scale (0‐1), indicating absence or presence. The assessment of systemic symptoms includes acute onset (0=absent, 1=present), floating pulse (0=absent, 1=present), tongue body (0=normal, 1=fresh red, 2=crimson), and tongue coating (0=thin white, 1=thick greasy, 2=yellow greasy). All TCM syndrome assessments will be independently performed by trained dermatologists with a TCM background. A total syndrome score will be calculated, and changes in the score before and after treatment will be compared to evaluate therapeutic efficacy. In this study, TCM syndrome scores will be assessed at baseline (week 0) and at weeks 1, 2, and 4. Details of TCM syndrome scores are shown in Multimedia Appendix 1.

### Safety Assessment

Before enrollment, all patients diagnosed with mild to moderate AD will undergo a standardized informed consent process, during which comprehensive information regarding the study objectives, potential benefits, and possible risks will be fully disclosed. An adverse event is defined as any unfavorable medical occurrence after treatment, including symptoms, signs, diagnosable diseases, or abnormalities in laboratory test results, regardless of whether a causal relationship with the study intervention is established. Participants will report all adverse events occurring during the 4-week treatment period. All reported events will be documented in case report forms (CRFs), together with precise timing and detailed clinical descriptions.

In accordance with clinical practice guidelines, any patients who experience a serious adverse event will be immediately withdrawn from the study and provided with free medical management as specified in the study protocol. These safety measures are designed to ensure rigorous data collection and safeguard participant well-being throughout the trial. Given the minimal risk associated with this study, an independent data monitoring committee will not be established.

### Withdrawal and Dropout

In accordance with the Declaration of Helsinki, participants may withdraw from the study at any time for any reason. All personal information will be kept strictly confidential, and reasons for withdrawal will be recorded in the CRFs.

### Data Collection and Management

This study will adopt a standardized data collection and management procedure. All study data will be collected using CRFs completed by dermatologists who have received unified training. The CRFs consist of six sections: (1) demographic characteristics, including age, sex, date of birth, marital status, and so forth; (2) medical history, including disease history, prior surgical treatments, allergy history, and family history of AD; (3) vital signs and physical examination, including height, weight, and BMI; (4) disease severity and treatment efficacy assessments, conducted at baseline (week 0), week 1, week 2, and week 4, including the EASI, IGA, DLQI, BSA, PNRS, POEM, and TCM syndrome scores; (5) laboratory examinations, including pregnancy testing, routine blood tests, routine urinalysis, and assessments of liver and renal function; and (6) safety and medication information, including prior medication use, concomitant medications, and adverse events.

In this study, a database will be established using EpiData (version 3.1; EpiData Association), with input validation rules defined for each variable, including data type, value ranges, and logical checks. Data entry will be performed independently using a double-entry method, followed by consistency checks between the 2 datasets. Any discrepancies will be resolved by referring to the original CRFs until complete agreement is achieved. The finalized database will be converted into SAS datasets, and data validation and logical checks will be conducted using SAS (version 9.4; SAS Institute) [18].

### Statistical Analysis

Statistical analyses will be performed using SAS (version 9.4). The primary analysis will follow the per-protocol principle, with supportive analyses conducted under the intention-to-treat framework including all randomized patients. Missing data will be handled under the missing-at-random assumption using sequential regression multiple imputation. This study is designed as an equivalence trial, with the primary end point being the proportion of patients achieving EASI50 at week 4. The prespecified equivalence margin (Δ) was set at 15% based on clinical considerations. Equivalence will be assessed using the 2-sided 95% CI approach: the difference in EASI50 response rates between groups will be estimated, and the corresponding 95% CI will be constructed using the chi-square test. Equivalence will be concluded if and only if the entire CI lies within the predefined margin of −15% to +15%. For intergroup comparisons among the 4 treatment groups, an overall test will first be performed. Subsequently, pairwise comparisons will be conducted where appropriate. Between-group comparisons will be performed using the Student *t* test (2-tailed) or Wilcoxon rank-sum test, as appropriate. For multiple pairwise comparisons, Bonferroni correction will be applied to control for type I error. Linear mixed-effects models will be applied for continuous outcomes, and generalized linear mixed models will be used for binary outcomes, with subject-specific random effects to account for within-subject correlation and to appropriately handle missing data. Categorical variables will be expressed as frequencies and percentages and compared using the chi-square test or Fisher exact test. In addition, a dose-response model will be constructed to characterize the dose-response relationship of granules and to explore the formulation conversion between granules and traditional decoction. Except for the equivalence testing described above, a 2-sided *P*<.05 will be considered statistically significant.

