### Blinding

This study is designed as an open-label trial, in which both the participants and the investigators will be aware of the treatment assignments. However, the outcome assessors and the statisticians will be blinded throughout the trial period to prevent potential information bias.

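### The only analysis-set rule, per-protocol leading and intention-to-treat supporting, is not limited to the equivalence test, so the dose comparisons and dose-response model could be led by a post-randomisation subset

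*Protocol article*

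**What the plan says.** All the relevant text is in the protocol article, mostly under Statistical Analysis.

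- Analysis sets: "The primary analysis will follow the per-protocol principle, with supportive analyses conducted under the intention-to-treat framework including all randomized patients".
- What the trial is for, two sentences later: "This study is designed as an equivalence trial, with the primary end point being the proportion of patients achieving EASI50 at week 4".
- Tests of difference: "For intergroup comparisons among the 4 treatment groups, an overall test will first be performed". Pairwise tests follow where appropriate, and "For multiple pairwise comparisons, Bonferroni correction will be applied to control for type I error". Mixed models are planned for continuous and binary outcomes.
- Modelling: "a dose-response model will be constructed to characterize the dose-response relationship of granules".
- Missing outcomes: "Missing data will be handled under the missing-at-random assumption using sequential regression multiple imputation".
- The one exception written into the section concerns the significance level and not the analysis set: "Except for the equivalence testing described above, a 2-sided *P*<.05 will be considered statistically significant".

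Under Blinding, "both the participants and the investigators will be aware of the treatment assignments"; outcome assessors and statisticians are blinded. The Sample Size section describes the two-thirds and one-tenth arms (50 patients each) as there to explore dose-response. The Introduction expects the model to define a minimum effective dose and a recommended range.

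**The concern.** The usual reason to lead with per-protocol in an equivalence trial is that departures from protocol can pull two arms together and so favour a finding of equivalence. That reason does not carry over to analyses that look for a difference. There, the comparison protected by randomisation is the one between all randomised patients in the arm assigned. Membership of a per-protocol set is settled after randomisation and can depend on the dose received and on how the patient is doing.

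Here that dependence is plausible. Patients and investigators know the arm, and one arm receives a tenth of the dose. A patient on that arm who is not improving has more reason than others to stop or to seek other treatment. If such patients leave the leading set, the low dose looks better than it is and the dose-response curve is flattened. If exclusions differ between equally effective arms, the tests of difference no longer hold their nominal 5% error rate. What is at stake is the dose-finding aim. Requiring intention-to-treat to agree on the equivalence interval would not settle which set leads the dose comparisons.

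**Working it through.** The plan gives no figure for this point. Its sample size (94 and 47 before dropout) concerns the equivalence pair only and does not bear on the choice of set. What follows is therefore an illustration.

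**Inputs from the document.** EASI50 of 90% on the standard dose; 100 patients on the standard dose and 50 on one-tenth; two-sided 0.05; Bonferroni over the 6 pairs of 4 arms, giving 0.05/6 = 0.0083.

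**Assumptions, none given in the document.** EASI50 of 70% on one-tenth, and the share e of non-responders excluded from the per-protocol set.

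**Formula.** With true response p, the per-protocol response is p / [p + (1 − p)(1 − e)]. Power is the exact binomial probability that the pooled chi-square test rejects, with arm sizes reduced by the exclusions.

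**All randomised, complete outcomes.** The gap is 90 − 70 = 20 points. Power is 86% at 0.05 and 67% at 0.05/6.

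**Non-responders excluded from the one-tenth arm only.** That arm has 0.30 × 50 = 15 non-responders.

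| e | Patients excluded | Per-protocol response | Gap | Power at 0.05 | Power at 0.05/6 |
|---|---|---|---|---|---|
| 20% | 3 (6% of arm) | 0.70/(0.70 + 0.30 × 0.8) = 74.5% | 15.5 | 69% | 44% |
| 40% | 6 (12% of arm) | 0.70/(0.70 + 0.30 × 0.6) = 79.5% | 10.5 | 41% | 20% |

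**The same 30% of non-responders excluded from both arms.** Standard dose: 0.90/(0.90 + 0.10 × 0.7) = 92.8%. One-tenth: 0.70/(0.70 + 0.30 × 0.7) = 76.9%. The gap is 15.9 points, and power at 0.05/6 is 54%. Attenuation does not need a different exclusion rule in each arm.

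**Half of those excluded are responders.** Excluding 5%, 10% or 20% of the one-tenth arm leaves gaps of about 19, 18 and 15 points. For 10%: (35 − 2.5)/45 = 72.2%, a gap of 17.8.

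**No true difference.** With 80% in both arms, excluding 10% of standard-dose and 40% of one-tenth-dose non-responders gives apparent rates of 81.6% and 87.0%. The test at 0.05 then rejects about 11% of the time, against 5.1% with no exclusions.

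**Cases that run the other way.**

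- If 10% of the standard-dose arm do not adhere and respond at 70%, intention-to-treat shows 0.9 × 90 + 0.1 × 70 = 88%, a gap of 18 points. Per-protocol shows 20.
- If 40% of one-tenth-dose non-responders take other treatment and all then respond, intention-to-treat shows 70 + 0.4 × 30 = 82%, a gap of 8 points with 30% power at 0.05. That is flatter than the 10.5 points when the same patients are excluded. If half of them respond, the intention-to-treat gap is 14 points.

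**The case against.** The strongest objection is textual. The sentence speaks of the primary analysis, and the sentences that follow tie what is primary to equivalence on EASI50 at week 4. The 4-group test, pairwise tests and models come later, and none is called primary. A reader might infer that the plan prescribes a per-protocol comparison of the doses. The document does not say so; that is one reading of a sentence whose scope is left open. On the narrower reading, what remains is that no set is named for the secondary and exploratory analyses, which an article may leave to the full analysis plan.

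Other points also stand. All-randomised analyses are planned, so the question is which of two results leads. The dose arms are exploratory, and the Discussion says that the optimal dose needs larger studies. The low-dose response and the exclusion shares are assumed, and the only attrition figure given is 5% dropout. Intention-to-treat is no clean benchmark either. Its 20 points and 86% power presuppose complete outcomes and no other treatment, and imputation under missing at random can itself overstate low-dose response if leaving depends on the unseen outcome.

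The objection does not remove the point. The article does fix a hierarchy, and the only role that it gives to all-randomised analyses is supportive. On either reading, nothing gives them the lead where differences between doses are tested, and nothing says which result governs if the two sets disagree.

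**Conclusion.** The point holds as a defect of scope: the one stated hierarchy is not confined to the analysis that justifies it. Applied to the dose comparisons and the dose-response model, it would put a post-randomisation subset in the lead in an open-label trial. Under the assumed 90% and 70%, a true 20-point gap would show as 15.5 to 10.5 points if 20% to 40% of one-tenth-dose non-responders were excluded. These sizes are illustrative and rest on rates that the document does not give.

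A reader might also infer that the dose effect will be flattened. The document does not support that: per-protocol can enlarge the gap as well as shrink it, depending on who is excluded and why. The uncertain direction is itself a reason to lead with the randomised comparison. The change should be made, but the choice of per-protocol for the equivalence interval is not faulted here.

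**What to change.** In the Statistical Analysis section, limit the leading per-protocol set to the decoction versus standard-granule equivalence interval. Then state that the 4-group overall test, the pairwise dose comparisons, the mixed models and the dose-response model are led by intention-to-treat (all randomised patients, in the arm assigned, with the imputation already planned), and that per-protocol is the sensitivity analysis for these.

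The cost is about one sentence. Both sets are already planned, no patients or data are added, and no patient had been recruited when the article was submitted. There is a small downside: the lead curve would describe the dose assigned and not the dose taken, and it would still depend on the missing-at-random imputation and on any use of other treatment. The per-protocol curve, reported alongside, covers part of that.

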### Sample Size

This study is designed as an equivalence clinical trial to compare the traditional decoction and the standard-dose granule of IFN-1, with the primary outcome being the proportion of patients with mild to moderate AD achieving EASI50 after 4 weeks of treatment. EASI50 is defined as the percentage of patients achieving ≥50% improvement in EASI score from baseline, reflecting the treatment’s effectiveness in skin lesion improvement. On the basis of previous studies, the EASI50 rate is expected to be 90% in both the traditional decoction group and the granule group at the standard dose. Setting the equivalence margin at Δ=15%, α=.05 (2-sided), and β=.20, the required sample sizes under a 2:1 allocation are 94 and 47, respectively. Considering a 5% dropout rate, the sample sizes are increased to 100 and 50 for the decoction group and the granule standard-dose group, respectively. To explore the dose-response relationship, we include a two-thirds dose granule group (n=50) and a one-tenth dose granule group (n=50). Additionally, 50 patients are added to the standard-dose granule group to strengthen the robustness of the findings. The final study therefore uses a 4-arm parallel design with an allocation ratio of 2:2:1:1 into traditional decoction (n=100), standard-dose granule (n=100), two-thirds dose granule (n=50), and one-tenth dose granule (n=50).

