### Randomization

This study is planned to use a stratified block randomization method with “study hospital” as the stratification factor. A total of 300 patients with mild to moderate AD will be randomly assigned in a 2:2:1:1 ratio to the traditional decoction group (n=100, 33.3%), standard-dose granule group (n=100, 33.3%), two-thirds dose granule group (n=50, 16.7%), and one-tenth dose granule group (n=50, 16.7%). The randomization scheme and implementation will be monitored by dedicated statisticians at the Clinical Research Center of Shanghai Skin Disease Hospital. Randomization codes will be generated by the same center and concealed in opaque, sealed envelopes. After recruitment screening, the envelope will be opened by study personnel, and the patient will receive the treatment corresponding to the assigned random number.

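### The primary 95% CI is specified only as coming from the chi-square test, which does not define an interval to hold against ±15 points; the score interval should be named

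*Protocol article*

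**What the plan says.** The Statistical Analysis section sets the decision rule: "Equivalence will be concluded if and only if the entire CI lies within the predefined margin of −15% to +15" percent. For the interval itself it says that "the corresponding 95% CI will be constructed using the chi-square test". It gives no variance formula and names no stratum for this interval.

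The Sample Size section supplies the planning values. Of the response rate it says that "the EASI50 rate is expected to be 90% in both the traditional decoction group and the granule group at the standard dose". The error rates and basic numbers are "α=.05 (2-sided), and β=.20, the required sample sizes under a 2:1 allocation are 94 and 47, respectively". Dropout is set at 5%, and the final arms are "traditional decoction (n=100), standard-dose granule (n=100), two-thirds dose granule (n=50), and one-tenth dose granule (n=50". The equivalence comparison is decoction against standard-dose granule, so 100 against 100.

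The Randomization section describes a "stratified block randomization method with “study hospital” as the stratification factor", and Study Design lists five hospitals.

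**The concern.** One interval decides the trial, and its method is stated in words that do not fix it. The Pearson chi-square statistic compares the observed difference with zero. To judge a difference against a 15-point margin, one needs either a standard error placed around the estimate or a test inverted over a range of non-zero differences. At least three intervals fit the wording:

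- a Wald interval with unpooled variance;
- an interval using the pooled variance of the chi-square test;
- an inverted score chi-square interval, which is Miettinen-Nurminen.

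The first two can be too narrow on the side that matters when response is high, so they can declare equivalence slightly too often. If the choice is left until the data are in, a borderline result could turn on it, and the trial is open-label for participants and investigators.

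**Working it through.** **Inputs.** Margin 0.15, two-sided 95% CI (2.5% at each limit), 90% response in both arms, 5% dropout and 100 per arm all come from Sample Size and Statistical Analysis. Five hospitals comes from Study Design. Assumptions of this check: a 95% response rate, equal hospitals with 20 patients per arm each, and the hospital response rates used in step 5.

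**1. The plan's own figure.** With ratio 2:1, the decoction arm needs (1.960 + 0.842)² × (0.9×0.1 + 2×0.9×0.1) / 0.15² = 7.849 × 0.27 / 0.0225 = 94.19, and the granule arm half of that, 47.09. This agrees, within rounding, with the stated 94 and 47. The calculation is a normal approximation and does not tell us which interval is meant. The final arms are 100 and 100, or 95 and 95 after 5% dropout (100 × 0.95).

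**2. The three readings.** With d = p₁ − p₂:

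- Wald: d ± 1.96 √[p₁(1−p₁)/n₁ + p₂(1−p₂)/n₂].
- Pooled: d ± 1.96 √[p(1−p)(1/n₁ + 1/n₂)], p being the overall rate.
- Miettinen-Nurminen: all δ with |d − δ| / √V(δ) ≤ 1.96, where V(δ) is the unpooled variance at the maximum likelihood rates constrained to differ by δ, times N/(N−1), with N = n₁ + n₂.

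**3. They can disagree.** Take 95 and 88 responders out of 100 each, so d = 0.07.

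- Wald SE = √(0.000475 + 0.001056) = 0.0391; upper limit 14.67 points: equivalent.
- Pooled SE = √(0.915 × 0.085 × 0.02) = 0.0394; upper limit 14.73 points: equivalent.
- Miettinen-Nurminen upper limit 15.50 points: not equivalent.

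When both true rates are 90%, Wald and Miettinen-Nurminen reach different verdicts in 3.5% of trials with 100 per arm and 6.1% with 95 per arm.

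**4. Error at the margin and power.** Each figure sums the two binomial distributions over every outcome for which the whole CI lies within ±0.15.

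| Per arm | True rates | Wald | Pooled | Miettinen-Nurminen |
|---|---|---|---|---|
| 95 | 90 v 75 (error) | 2.79% | 2.75% | 2.37% |
| 95 | 95 v 80 (error, assumed rate) | 3.50% | 2.98% | 2.14% |
| 100 | 90 v 75 (error) | 2.71% | 2.64% | 2.37% |
| 100 | 95 v 80 (error, assumed rate) | 3.23% | 2.97% | 2.34% |
| 95 | 90 v 90 (power) | 86.6% | 84.8% | 80.5% |
| 100 | 90 v 90 (power) | 88.0% | 87.0% | 84.5% |

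**5. Hospital strata.** The share of variance removed by stratifying is the between-hospital variance of the response rate divided by p(1−p) = 0.09.

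- Hospitals alike: 0%.
- Rates 85, 87.5, 90, 92.5, 95: 0.00125 / 0.09 = 1.4%.
- Rates 80, 86, 92, 94, 98: 0.0040 / 0.09 = 4.4%.
- Rates 72, 88, 94, 97, 99 (extreme): 0.00948 / 0.09 = 10.5%.

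In 300,000 simulated trials per scenario with 100 per arm, the unstratified Wald error went from 2.7% with identical hospitals down to 2.3% in the extreme case; unstratified Miettinen-Nurminen went from 2.4% to 2.0%. Stratified Miettinen-Nurminen stayed at about 2.4%. Its power in the four scenarios was 84.0, 84.0, 84.3 and 85.4%, against 84.5, 84.7, 85.5 and 86.6% unstratified.

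**The case against.** The best defence is that the effect is small where the trial was planned. At 90% versus 75% the Wald and pooled readings exceed 2.5% by only 0.1 to 0.3 points, and two-sided Wald coverage was 94.6 to 94.8% in the cases checked. The 95% rate is not in the protocol. If the authors meant the inverted score chi-square, there is no excess at all. All of this stands and limits the size of the point. It does not remove it: the text does not say which interval is meant, and the readings can split on the same data.

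A reader might infer three stronger things that the documents do not support:

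- *That leaving out the hospital strata inflates the error rate.* The direction is the reverse: with blocked randomisation by hospital, an unstratified interval is slightly too wide when hospitals differ. The excess comes from the type of interval.
- *That stratifying yields free precision.* The variance saving is about 0 to 4% under moderate assumed hospital differences, and the protocol gives no figure for those differences. With 20 per arm per hospital, the stratified score interval had slightly lower power than the unstratified one in every scenario.
- *That the larger distortions possible with a 50-patient arm bear on the main result.* The Sample Size section sets equivalence between the two 100-patient arms; the smaller arms are there for the dose-response question.

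The article also condenses a fuller plan, so silence on strata is not in itself a fault. The interval method is different: it is stated, and stated in a way that does not determine the result.

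**Conclusion.** The point holds as a badly specified method with a modest effect. The clause names a test of zero difference where an interval for a risk difference is needed. Under the Wald or pooled reading, and with 95 per arm, the error at the margin is 2.8% or 2.75% at the planned 90% and 3.5% or 3.0% if response were 95%. Miettinen-Nurminen stays below 2.5% in both cases (2.4% and 2.1%). These figures rest on independent binomial responses, 5% loss from the primary per-protocol comparison and, for the second pair, a response rate that this check assumes. Since 90% is itself only a planning value, rates somewhat above it are a reasonable stress test, not a forecast. The hospital stratum is a secondary matter of matching the analysis to the design and does not drive the error excess.

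**What to change.** In Statistical Analysis, replace the chi-square clause with: *95% CI for the risk difference by the Miettinen-Nurminen score method*. Add how hospital is taken into account, with the stratified version either as the primary analysis or as a sensitivity analysis, and state power under the interval chosen.

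The edit is one or two sentences. According to the abstract, nobody had been recruited at submission and analysis is due from March 2027, so it can be settled before data are seen.

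The cost is power. At 90% in both arms it falls by 6.1 points with 95 per arm (86.6% to 80.5%) and by 3.5 points with 100 per arm (88.0% to 84.5%). Both remain at or above the planned 80%, but at 95 per arm only 0.5 points are in hand. The stratified version was checked at 100 per arm only (84.0% with identical hospitals). If it is made primary, its power at 95 per arm should be confirmed first, and exclusions beyond 5% from the per-protocol set would use up the reserve.

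### The named Student t test is fragile at 100 versus 50: if the smaller arm is 1.25 to 2 times as variable, secondary continuous comparisons run at about 7% to 11% error instead of 5%; naming Welch fixes this cheaply

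*Protocol article*

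**What the plan says.** In the protocol article, the Statistical Analysis section begins the four-arm comparisons with a global step: "For intergroup comparisons among the 4 treatment groups, an overall test will first be performed". Pairwise comparisons follow where appropriate, and the named tests are: "Between-group comparisons will be performed using the Student *t* test (2-tailed) or Wilcoxon rank-sum test, as appropriate". Multiplicity is handled by Bonferroni: "For multiple pairwise comparisons, Bonferroni correction will be applied to control for type I error". The number of comparisons is not given. The level outside the equivalence test is fixed: "a 2-sided *P*<.05 will be considered statistically significant".

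The same section also says "Linear mixed-effects models will be applied for continuous outcomes", with subject-specific random effects. It does not say whether the t test, the rank test or the mixed model decides a given pairwise contrast.

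The Sample Size section fixes the arms as "traditional decoction (n=100), standard-dose granule (n=100), two-thirds dose granule (n=50), and one-tenth dose granule (n=50".

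The text does not say whether the variance is pooled, gives no SD for any continuous outcome, and announces no confidence interval for a difference in means.

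**The concern.** The Student t test as usually defined estimates one common variance from both arms, weighted by degrees of freedom. With equal arms this does little harm when spreads differ. At 2:1 the larger arm dominates the pooled estimate, while the smaller arm contributes most of the real uncertainty. If the smaller arm is the more variable one, the standard error is too small and the test rejects too often. If it is the less variable one, the standard error is too large and power is lost.

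The exposed contrasts are those between either reduced-dose arm (50) and either full-dose arm (100), on DLQI, BSA, PNRS, POEM and the TCM syndrome score. Several of these scales have a floor at zero, and the Sample Size section expects 90% EASI50 response at standard dose. A less effective reduced dose could therefore leave scores further from the floor and more spread out. That is a reason to guard against unequal variance, not evidence that it will occur.

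**Working it through.** **Plan's own figure.** There is none for a continuous outcome. The 94 and 47 in the Sample Size section belong to the binary EASI50 comparison.

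**Inputs.** Arms of 100, 100, 50 and 50 (Sample Size). Two-sided 5% and Bonferroni (Statistical Analysis). Assumed here: normal data, equal means, six pairs (level .05/6 = 0.83%) or three against one reference (.05/3 = 1.67%), and r = SD of the 50-patient arm divided by SD of the 100-patient arm, taken over a range.

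**Step 1: which pairs are unbalanced.** Each of the two arms of 100 against each of the two arms of 50 gives 2 × 2 = 4 of the 6 pairs. The other two pairs are 100:100 and 50:50.

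**Step 2: pooled standard error over true standard error at 100 versus 50.** With the larger arm's SD set to 1:

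ratio = sqrt{ [(99 + 49r²)/148 × (1/100 + 1/50)] / (1/100 + r²/50) }

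For r = 1.5: (99 + 110.25)/148 = 1.414; × 0.03 = 0.0424; true variance 0.01 + 0.045 = 0.055; sqrt(0.0424/0.055) = 0.878. For r = 1.25 and 2.0 the ratio is 0.929 and 0.815. The pooled standard error is thus about 7%, 12% and 18% too small.

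**Step 3: error of one comparison.** In large samples this is 2Φ(−z × ratio). At 5% (z = 1.960) it is 6.9%, 8.5% and 11.0% for r = 1.25, 1.5 and 2.0. At .05/6 (z = 2.638) it is 1.4%, 2.1% and 3.2%. Simulation at 100 versus 50 with 1,000,000 replicates agrees:

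| r | Pooled t, error at 5% | Multiple of nominal at .05/3 | Multiple of nominal at .05/6 | Welch, error at 5% |
|---|---|---|---|---|
| 0.50 | 1.7% | 0.21 | 0.17 | 5.0% |
| 0.67 | 2.6% | 0.40 | 0.33 | 5.0% |
| 0.80 | 3.5% | 0.60 | 0.55 | 5.0% |
| 1.00 | 5.0% | 0.99 | 0.99 | 5.0% |
| 1.25 | 6.8% | 1.55 | 1.71 | 5.0% |
| 1.50 | 8.5% | 2.12 | 2.45 | 5.0% |
| 2.00 | 11.0% | 3.07 | 3.79 | 5.0% |

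Results at 95 versus 48 (after 5% dropout) are almost the same. Equal-sized pairs stay at 5.0% to 5.1% even at r = 2, so the cause is the unequal allocation.

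**Step 4: family-wise error with six Bonferroni comparisons.** Four arms, equal means throughout, 300,000 replicates, overall test taken as a classical F test at 5%. Ranges run over r from 1.25 to 2.

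| Scenario | Bonferroni alone | After the overall test |
|---|---|---|
| All SDs equal | 0.041 | 0.036 |
| One 50-patient arm more variable | 0.049–0.067 | 0.043–0.055 |
| Both 50-patient arms more variable | 0.057–0.096 | 0.050–0.084 |

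The F test itself rejects at 6.2% to 10.6% (one arm) or 7.1% to 12.7% (both). With Welch pairwise tests the Bonferroni family-wise error, without the overall test, is 0.036 to 0.041 in all these scenarios.

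**Step 5: the rank-sum alternative.** At 95 versus 48 it rejects in 6.1%, 6.8% and 8.3% of runs at r = 1.25, 1.5 and 2.0 (8,000 runs). It dampens the effect but does not remove it if the question is about location.

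**Step 6: cost of Welch when variances are equal.** At 95 versus 48 and a difference of 0.5 SD, power at 5% is 0.800 for Welch against 0.803 for the pooled test. A repeat with 4,000,000 replicates gives the same loss of 0.3 points at 5% and about 0.7 points at .05/6 (0.553 against 0.559).

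**The case against.** The strongest reply is that the article does not fix the defect. It names the t test or the rank-sum test as appropriate, assigns mixed models to continuous outcomes, and never mentions pooling. The choice between pooled and Satterthwaite variance is often left to the analysis plan. This stands in part: a reader might infer that the pooled t test is the settled analysis of every continuous outcome, and the text does not support that. Even so, the article names a specific test whose standard form pools, in a design where pooling is fragile. The rank-sum option does not fully cure this, and a mixed model with one common residual variance could share the weakness.

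Second, no SD is given, and all arms receive the same background topical treatment, so spreads may be similar. This stands in full: the SD ratio is an assumption, and the error vanishes or reverses at other values.

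Third, if a reduced dose spreads out because it works less well, the means differ and a rejection is not a type I error. This is fair for that contrast. The standard error would still be too small by the same fraction, so the precision of the comparison would be overstated.

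Fourth, a reader might infer that Bonferroni control fails by the per-comparison multiples. It does not. Bonferroni targets the family-wise rate, and with one variable small arm and the overall test in place that rate is 0.043 to 0.055, close to 0.05.

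Fifth, a reader might infer that the trial's reported 95% intervals would cover only about 89% to 93%. That would describe a pooled t interval at r = 1.25 to 2, but none is announced. The interval the section specifies is for response rates: "the difference in EASI50 response rates between groups will be estimated, and the corresponding 95% CI will be constructed using the chi-square test".

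**Conclusion.** The point holds as a minor, conditional one. Four of the six arm pairs are 2:1, and the named Student t test, read in its pooled form, is not robust there. If the 50-patient arm has an SD 1.25 to 2 times that of the 100-patient arm, a single comparison at nominal 5% runs at about 7% to 11%, and at .05/6 at about 1.7 to 3.8 times nominal (1.6 to 3.1 times at .05/3). The family-wise error after the overall test is about 0.043 to 0.084. With equal SDs there is no error; with a less variable small arm the test is conservative.

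These sizes rest on normal data, equal means and an SD ratio for which the documents give no figure. Only secondary continuous outcomes are touched. The primary EASI50 equivalence comparison is binary and 100:100. A reader might also infer that the dose-response objective rests on these t tests, but the Statistical Analysis section gives that objective a separate dose-response model.

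**What to change.** In the Statistical Analysis section, name the Welch (Satterthwaite, unequal-variance) t test for pairwise comparisons of continuous outcomes and Welch ANOVA for the overall test. Where the linear mixed model supplies the same contrasts, let the residual variance differ by arm. If a confidence interval is reported for a mean difference, use the Welch interval or the one from that mixed model.

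This is a change of wording using options available in SAS, and the analysis is not due to start until March 2027. The statistical price is about 0.3 percentage points of power at the 5% level if the variances turn out equal, and slightly more at a Bonferroni level.
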